# Effects of cortico-cortical paired associative stimulation based on multisensory integration to brain network connectivity in stroke patients: study protocol for a randomized doubled blind clinical trial

**DOI:** 10.1186/s12883-023-03218-2

**Published:** 2023-04-28

**Keywords:** Stroke, Transcranial magnetic stimulation, Spike-timing dependent plasticity, Cortico-cortical paired-association stimulation, Primary visual cortex, Primary motor cortex, Multisensory integration

## Abstract

**Introduction:**

: Brain has a spontaneous recovery after stroke, reflecting the plasticity of the brain. Currently, TMS is used for studies of single-target brain region modulation, which lacks consideration of brain networks and functional connectivity. Cortico-cortical paired associative stimulation (ccPAS) promotes recovery of motor function. Multisensory effects in primary visual cortex(V1) directly influence behavior and perception, which facilitate motor functional recovery in stroke patients. Therefore, in this study, dual-targeted precise stimulation of V1 and primary motor cortex(M1) on the affected hemisphere of stroke patients will be used for cortical visuomotor multisensory integration to improve motor function.

**Method:**

This study is a randomized, double-blind controlled clinical trial over a 14-week period. 69 stroke subjects will be enrolled and divided into sham stimulation group, ccPAS low frequency group, and ccPAS high frequency group. All groups will receive conventional rehabilitation. The intervention lasted for two weeks, five times a week. Assessments will be performed before the intervention, at the end of the intervention, and followed up at 6 and 14 weeks. The primary assessment indicator is the ‘Fugl-Meyer Assessment of the Upper Extremity ’, secondary outcomes were ‘The line bisection test’, ‘Modified Taylor Complex Figure’, ‘NIHSS’ and neuroimaging assessments. All adverse events will be recorded.

**Discussion:**

Currently, ccPAS is used for the modulation of neural circuits. Based on spike-timing dependent plasticity theory, we can precisely intervene in the connections between different cortices to promote the recovery of functional connectivity on damaged brain networks after stroke. We hope to achieve the modulation of cortical visuomotor interaction by combining ccPAS with the concept of multisensory integration. We will further analyze the correlation between analyzing visual and motor circuits and explore the alteration of neuroplasticity by the interactions between different brain networks. This study will provide us with a new clinical treatment strategy to achieve precise rehabilitation for patient with motor dysfunction after stroke.

**Trial registration:**

This trial was registered in the Chinese Clinical Trial Registry with code ChiCTR2300067422 and was approved on January 16, 2023.

## Introduction

Stroke accounts for 10% of global deaths, and the lifetime risk of stroke is estimated to be 24.9% for people over the age of 25 years worldwide. This means that one in four people will have a stroke, with the risk of ischemic stroke being higher than that of hemorrhagic stroke [1–3].

Stroke is the leading cause of death in China, and its burden has been increasing over the past three decades. There is a gradient of stroke incidence from north to south, with the highest incidence of stroke in northern and central China [1, 4]. The primary consequence of stroke for patients is the remaining motor dysfunction, which impedes their capacity to relearn daily living activities and work-related tasks [5, 6].

Clinically, neurorehabilitation therapies have been shown to improve the prognosis of stroke patients, but functional recovery can still be inadequate. Structural changes in the brain resulting from the stroke can severely impact patients’ prognosis and ability to recover functionally. [7]. Focal neurological deficits resulting from structural changes in the brain are associated with imbalanced tissue function and disordered neurophysiological responses in the affected primary cortex [5]. Studies have shown that neurological deficits may arise from alterations in both local and distant white matter tracts, as well as from disrupted neural interactions between widely distributed networks [8]. Previous studies have analyzed functional Magnetic Resonance Imaging (fMRI) data from thousands of healthy individuals and constructed a human brain connectome [9]. These studies have revealed that different symptoms can be caused by lesions in the same brain region, and conversely, the same symptoms can be caused by injuries in different locations. Briefly, specific compensatory patterns of structure and function in neural network interactions are associated with central plasticity and clinical improvement [10]. The analysis of brain structural or functional networks can help to identify the specific networks that different brain regions belong to, which can inform the development of precise treatments for stroke patients.

Recent developments in brain assessment methods and statistical techniques have led to increased research into the structural and functional effects of stroke on the brain [11]. The normal functioning of the brain is dependent on a dynamic equilibrium between the specialized functions of local brain regions, the transmission of information through neural circuits, and the integration of information across large-scale functional neural networks [12, 13]. Previous research has demonstrated that focal deficits can impact the entire brain and its network properties, leading to the idea that stroke can be seen as a disruption of brain networks [8]. Therefore, it is worth exploring whether brain dysfunction can be restored by regulating the networks.

The optimal control theory of movement requires the integration of multiple sensory systems, such as vision and proprioception. The effective functioning of multiple sensory systems is crucial for maintaining motor function. Relevant studies have suggested that visual compensation can facilitate the recovery of motor function in patients with stroke. [14]. Additional studies have demonstrated that peripheral co-excitation can spread centrally within auditory and somatosensory networks, while also eliciting brain responses in other networks involved in multisensory integration [15]. The brain has a powerful ability to automatically and simultaneously process and integrate sensory information. Integrating information from multiple sensory modalities contributes to the recovery of stroke patients in motor relearning by detecting, discriminating, and recognizing sensory stimulation [16]. While, the brain areas related to multisensory processing and those related to motor control are located in separate networks.

Previous studies have demonstrated that repetitive transcranial magnetic stimulation (rTMS) targeting specific cortical areas can effectively modify neural circuits, even the networks [17]. Transcranial magnetic stimulation (TMS) is a method of delivering electrical stimulation through the scalp [10]. Single-pulse TMS is always used to assess the activity threshold of the brain, whereas rTMS is used to induce changes in brain activity, such as affecting blood flow and metabolism in some brain regions, modulating neurotransmitter expression in the brain, and preventing long-term damage to brain tissue from delayed neurological death caused by ischemia. [18–21]. In the last few years, researchers have made considerable progress in using TMS for stroke research [22, 23]. The effect of rTMS on the excitability of networks is considered a promising strategy for the rehabilitation of stroke patients [24, 25].

The mechanism of rTMS is associated with information processing in the nervous system, which includes synaptic excitation, synaptic inhibition, and synaptic plasticity of neurons [23, 26]. The neuroplasticity with synaptic changes based on long-term potentiation and depression plays a crucial role in functional recovery after stroke [27, 28]. As an intriguing therapeutic stimulation modality of TMS, cortico-cortical paired associative stimulation (ccPAS) modulates cortical plasticity by stimulating different cortices using dual coils, which allows for the direct activation of the cortico-cortical pathway connecting two areas [29, 30]. Meanwhile, it was unexpected to find that ccPAS is consistent with spike-timing dependent plasticity (STDP), a theory related to the precise timing of pre- and post-synaptic action potentials, by manipulating the interstimulus interval between the two stimulus points [31, 32]. Then, researchers began to investigate the bidirectional modulation of cortical plasticity using different ccPAS protocols [33–35]. The use of STDP theory in TMS research is gradually increasing. In one study, investigators used a ccPAS protocol to induce bidirectional cortico-cortical associative plasticity in the posterior parietal cortex (PPC)-M1 network. When PPC preceded M1 stimulation (ccPAS + 5 ms), there was a long-lasting decrease in the excitability of M1, indicating a long-term depression (LTD)-like effect. Conversely, when PPC followed M1 stimulation (ccPAS − 5 ms), there was a long-lasting increase in the excitability of M1, indicating a long-term potentiation (LTP)-like effect [34, 36].

As a result, ccPAS could be utilized to modulate the information processing between different brain networks. The application of ccPAS between different networks would help us better understand the neurophysiological substrates of complex sensorimotor interactions and multisensory integration [30].

Naturally, our aim was to use STDP-based ccPAS to investigate whether the integration of sensory and motor systems, or networks, can enhance motor function recovery in stroke patients. In this study, we selected M1 and V1 as the stimulation targets for the motor and visual networks. M1 is a crucial component of the motor network and plays a significant role in movement execution. Previous TMS studies have used M1 as a stimulation target, demonstrating that its activation can improve motor function recovery [37]. Multisensory effects in V1 can directly influence behavior and perception, which can facilitate motor functional recovery in stroke patients [38]. Additionally, researchers conducted a ccPAS study of the visual motion area (V5) and V1 [39], where they found that: (1) paired associative TMS of human V5-V1 affects the perception of motion coherence and (2) TMS plastic strengthening of reentrant V5-V1 connections enhances motion sensitivity. Physiologically, there is enough distance between the skin mapping points of V1 and M1 to allow for the placement of a dual coil, which is conducive to achieving precise stimulation in this study.

The results of the current study can be used to determine whether paired associative stimulation of V1 and M1 based on the STDP theory can effectively restore motor function in stroke patients. Furthermore, it can help to elucidate the mechanisms underlying central plasticity changes during the intervention and shed light on the impact of interactions between different brain networks on brain plasticity.

## Methods and analysis

### Study design

This study is a double-blind randomized controlled trial, and the protocol is registered with the Chinese Clinical Trials Registry. A total of 69 participants will be divided 1:1:1 into three groups. The control group will receive conventional treatment plus sham ccPAS, the ccPAS low-frequency group received conventional treatment plus 0.2 HZ of ccPAS, and the ccPAS high-frequency group will receive conventional treatment plus 5 HZ of ccPAS.

Each group will receive the intervention five times per week for two weeks. The researcher will follow up with subjects in week six and week fourteen respectively (as shown in Fig. 1 and Table 1).T The primary outcome measure will be the ‘Fugl-Meyer Assessment of the Upper Extremity (FMA-UE)’, secondary outcomes will include ‘The line bisection test’, ‘Modified Taylor Complex Figure (MTCF)’, ‘NIH stroke scale (NIHSS)’, and’ functional Magnetic Resonance Imaging(fMRI)’ as well as ‘Diffusion tensor imaging (DTI)’.

**Fig. 1 Fig1:**
[figure not shown]
Flow diagram of study design. ccPAS, Cortical-cortical paired associative stimulation; FMA-UE, Fugl-meyer assessment of upper extremity; MTCF, Modified Taylor Complex Figure; NIHSS, National Institutes of Health Stroke Scale; fMRI, functional Magnetic Resonance Imaging; DTI, Diffusion tensor imaging

**Table 1 Tab1:** Participant timeline

Activity			Study Stuff		Study Period						
				Prestudy	0 week	1 week	2 weeks	2 weeks end	6 weeks end	10 weeks end	
Preparation	Sample size calculation		Investigator A	X							
	Eligibility screen		Investigator B	X		X	X	X	X	X	
	Medical information		Investigator B	X							
	Informed consent		Investigator B	X							
	Random allocation		Investigator B	X							
Intervention	ccPAS Low frequency Group	Conventional therapy	Doctor B + Therapist			X	X				
		0.2 HZ ccPAS	Investigator C			X	X				
	ccPAS High frequency Group	Conventional therapy	Doctor B + Therapist			X	X				
		5 HZ ccPAS	Investigator C			X	X				
	control Group	Conventional therapy	Doctor B + Therapist			X	X				
		sham-ccPAS	Investigator C			X	X				
Assessment	Primary outcome	FMA-UE	Assessor A		X			X	X	X	
	Secondary outcomes	The Line bisection test	Assessor B								
		MTCF	Assessor B		X			X	X	X	
		NIHSS	Assessor B		X			X	X	X	
		fMRI	Imaging doctor		X			X	X	X	
		DTI	Imaging doctor		X			X	X	X	
Statistical analysis			Investigator A					X		X	

ccPAS, Cortical-cortical paired associative stimulation; FMA-UE, Fugl-meyer assessment of upper extremity; MTCF, Modified Taylor Complex Figure; NIHSS, National Institutes of Health Stroke Scale; fMRI, functional Magnetic Resonance Imaging; DTI, Diffusion tensor imaging.

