### Recruitment and sample selection

Subjects will be recruited by the Department of Rehabilitation Medicine, Yueyang Hospital, Shanghai University of Traditional Chinese Medicine,based on strict inclusion and exclusion criteria. Those who meet the criteria will be asked to sign an informed consent form.

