### Exclusion criteria [42]

Contraindicated implants for MRI and TMS in vitro and in vivo;History of epilepsy, psychiatric disorders, or other serious cognitive or emotional disorders;History of medications that affect the central nervous system;Pregnant or lactating women;

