### Randomization and allocation concealment

A random number table will be generated by SPSS 25.0 to create random assignment cards. These cards will then be placed in opaque envelopes with envelope serial numbers connected to the card serial numbers. Participants will be randomly assigned codes based on the order in which they are seen. The grouping specified by the card inside the envelope will determine which group each participant will be assigned to, with each group consisting of 23 participants: a control group, a ccPAS low-frequency group, and a ccPAS high-frequency group. The grouping information will be kept confidential from the patients, their families, therapists, evaluators, and statistical analysts. Patient treatment information will be sent to the researcher one day prior to the treatment.

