### Blinding

Each participant will sign a written confidentiality agreement to ensure that information is not shared with others. Randomization of patients will be done remotely by a person who will not be involved in the rest of the trial process. Patients who meet the inclusion criteria will undergo a first basic assessment by a person dedicated to the assessment after signing the informed consent form.

Routine rehabilitation will be done by a physical therapist, an occupational therapist, and a speech therapist in the rehabilitation medicine department. ccPAS treatment will be done by a dedicated researcher, following the given parameters.

The two-week post-intervention assessment will be completed by a second assessor. Follow-up will be done by a third assessor. The data from all assessments will be analyzed by a dedicated data analyst, who will only be provided with the data results for each group without knowing the specific group allocation.

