### Intervention

Subjects will receive regular rehabilitation, including physiotherapy, occupational therapy, and speech and language therapy. Brain areas will be localized using the LOCALITE TMS Navigator system, which will rely on the patient’s magnetic resonance structural images to localize the M1 and V1 [44]. Patients will receive ccPAS treatment with a MagTD magnetic field stimulator from Wuhan Iredell Medical Equipment New Technology Co.

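### Table 1 places random allocation before the week-0 baseline and MRI, so the baseline is taken after assignment and a failed scan becomes a post-randomisation dropout

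*Protocol article*

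**What the plan says.** Table 1 of the protocol article has one mark in the row "Random allocation". It lies in the Prestudy column, together with medical information, informed consent and the first mark of the row "Eligibility screen". The eligibility row has no mark at week 0. Its next marks are at week 1 and week 2, the two treatment columns, and then at the later visits.

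The first marks for FMA-UE, MTCF, NIHSS, fMRI and DTI are at week 0. No MRI is marked before that.

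The text adds the following:

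- Recruitment and sample selection: "Those who meet the criteria will be asked to sign an informed consent form".
- Exclusion criteria: these include "Contraindicated implants for MRI and TMS in vitro and in vivo".
- Blinding: eligible patients "will undergo a first basic assessment by a person dedicated to the assessment after signing the informed consent form". The order relative to allocation is not given.
- Randomization and allocation concealment: envelopes are used in the order in which patients are seen, "with each group consisting of 23 participants". No visit is named for opening the envelope. Group membership is withheld from patients and evaluators, among others, and a patient's treatment details reach the treating researcher the day before treatment.
- Intervention: M1 and V1 are found with a navigation system "which will rely on the patient’s magnetic resonance structural images to localize the M1 and V1".
- Dropout criteria: failure to complete the planned treatment is listed as a reason for dropout.

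**The concern.** A trial normally assigns the arm as late as it can: after the baseline is recorded and after it is known that the patient can receive the allocated treatment. Table 1 reverses this for two things.

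First, the baseline FMA-UE is the reference for all the within-group comparisons in the Behavior statistical analysis section. If it is recorded after assignment, its independence from the arm rests on masking. If it is recorded before, that independence follows from the order of events.

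Second, a usable structural MRI is needed before either coil can be placed. If the scan fails after allocation, a patient who could have been a screen failure is instead a randomised patient without treatment, and the dropout criteria then apply. This is an avoidable post-randomisation loss. The same holds if the targets cannot be located or the active motor threshold (AMT) cannot be measured. The article describes both steps only within the intervention, gives them no row in Table 1, and has no eligibility criterion that requires a measurable motor evoked potential.

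**Working it through.** **Order of events.** Reading the columns of Table 1 from left to right:

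| Step | Column in Table 1 |
|---|---|
| Eligibility screen (first), consent, random allocation | Prestudy |
| First FMA-UE, MTCF, NIHSS, fMRI, DTI | Week 0 |
| Next eligibility mark, first ccPAS or sham session | Week 1 |
| Target localisation, AMT measurement | No row |

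No sentence in the text changes this order. The Blinding section ties the first assessment to consent only, the Abstract places it before the intervention, and the Randomization section names no visit. Allocation before baseline and before the first MRI is therefore the only order that the article states.

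**The plan's sample size.** Inputs from the Sample size calculation section: three groups, means 8.11, 6.87 and 17.62, SD 8.83, α = 0.025, power 0.90, dropout 20%.

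- Grand mean = (8.11 + 6.87 + 17.62)/3 = 10.867.
- Sum of squared deviations = 7.599 + 15.973 + 45.607 = 69.18.
- Noncentrality λ = n × 69.18/8.83² = n × 69.18/77.97 = 0.887n, with 2 and 3n − 3 degrees of freedom.
- The smallest n with power of at least 0.90 is 18 per group (power 0.902), or 54 in total. This agrees with the plan.
- Dropout: 18/(1 − 0.20) = 22.5, rounded up to 23 per group, or 69 in total. This also agrees.
- Allowance: 69 − 54 = 15 patients, 5 per group.

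**Possible size of the loss.** The documents give no failure rate. Assume that 5% to 10% of allocated patients prove untreatable at the scanner, at localisation or at threshold finding:

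- 0.05 × 69 = 3.45 and 0.10 × 69 = 6.9, so about 3 to 7 patients.
- Share of the allowance: 3.45/15 = 23% to 6.9/15 = 46%.
- Per group: 0.05 × 23 = 1.15 to 0.10 × 23 = 2.3, so about 1 to 2 patients.

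Power at α = 0.025 by evaluable patients per group, with the same formula:

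| Evaluable per group | Power |
|---|---|
| 23 (no loss) | 0.966 |
| 22 | 0.957 |
| 21 | 0.947 |
| 20 | 0.935 |
| 18 (full 20% allowance used) | 0.902 |
| 17 (one more) | 0.881 |
| 16 (two more) | 0.855 |

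Power falls below 0.90 only if these losses are added to a full 5 per group from other causes.

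**The case against.** The strongest reply is that a condensed table is being read too literally. The Prestudy column also holds the sample size calculation, which is not a patient event, and the order within the column is not given. The allocation mark could mean preparing the sequence and envelopes, and the flow diagram, which is not available here, may show the order. This is possible. But the same column holds consent and screening, which are patient events. If the mark means only preparation, Table 1 shows no time at which patients are assigned. On either reading the article needs the same correction.

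Several stronger inferences are tempting, and the objection to them stands:

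- *Patients are allocated before MRI or TMS suitability is checked.* Not supported. Implant contraindications are an exclusion criterion, and the criteria are to be met before consent is sought. What comes after allocation is obtaining the scan. Localisation and threshold finding have no stated time.
- *Nothing stops an unsuitable patient from being treated.* Not supported. The eligibility row has a mark at week 1, and a patient without a usable MRI could not be navigated. Both checks still come after assignment.
- *The baseline is biased.* Not shown. Evaluators and patients are not told the group. The article does disagree with itself on who allocates: Table 1 names the investigator who also screens and takes consent, while the Blinding section says "Randomization of patients will be done remotely by a person who will not be involved in the rest of the trial process". That needs its own reconciliation, but it does not show that a baseline assessor knows the arm.
- *Losses would differ by arm.* No basis is given. The Control group section says that everything apart from the coil follows the low-frequency group.
- *Each such patient costs a place that cannot be refilled.* The article fixes 23 per group and mentions no replacement, but it does not rule replacement out.

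**Conclusion.** The point holds in a limited form. Table 1 puts assignment before the baseline assessments and before the first MRI, and no other statement in the article corrects that. The consequences are a baseline whose protection depends on masking, and avoidable dropouts among patients whose week-0 scan cannot be used.

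The expected size is modest. About 3 to 7 of 69 patients rests wholly on the assumed 5% to 10% failure rate. The planned allowance covers that number unless the full 20% dropout also occurs, in which case power would be about 0.88 with one further loss per group and 0.86 with two. The main gain from a change is fewer exclusions after randomisation; protection of power is secondary. It is worth making because it is cheap, and not because the trial is otherwise compromised.

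**What to change.** Move the allocation mark in Table 1 from Prestudy to the end of week 0, and add an eligibility mark at week 0. In Randomization and allocation concealment, state that the next envelope is opened only when consent, the baseline assessments and a usable MRI are complete and eligibility has been reconfirmed. Where no extra visit is needed, also confirm before allocation that both targets can be located and that the AMT can be measured. If the sponsor prefers the present order, the article should state it in the text and give the reason.

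The cost is one table correction and one or two sentences. The baseline assessments and MRI are already scheduled before the first session, and a later allocation fits the rule that treatment details are passed on the day before treatment. Localisation and threshold finding are not scheduled before that session, so bringing them forward adds a short measurement. That is why they are proposed only where no visit is added.
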